### Randomization

Participants will be randomly assigned to either the rTMS or the PAiT arm. Randomization will be done via Castor EDC and will be stratified for treatment center. We will use block randomization using random sequences of block sizes of 2, 4, and 6. This approach ensures treatment assignment balance within each complete block and minimizes the imbalance of group sizes within clinical centers, thus correcting for confounding from possible differences between treatment sites (such as differences in experience with rTMS). In addition, before the start of the trial, we will note patient’s preferred treatment, that is, standard 10 Hz rTMS or PAiT. The expected study duration is 48 months, and inclusion of patients started in February 2024.

### Intervention

The PAiT protocol, modeled after the SNT protocol [12], consists of 5 days of treatment in which a total of 90,000 magnetic pulses are given over 50 sessions (10 sessions per day, 50 minutes ISI). iTBS at 90% of the resting motor threshold corrected for cortical depth will be administered to the location within the left DLPFC showing the strongest anticorrelation with the sgACC. This is achieved using participant‐specific, resting state–fMRI‐guided neuronavigation. The coordinates within the DLPFC most anticorrelated with the sgACC are identified using the seedmap- and cluster-based method described by Cash et al [18]. The cluster threshold is set to 2.5%, meaning 2.5% of the most anticorrelated voxels are retained in the DLPFC before clustering. The center of gravity of the largest cluster is defined as the target coordinate. The target coordinate and corresponding stimulation site are located for each individual using neuronavigation software. The resting motor threshold is corrected for cortical depth at the stimulation site using the formula described by Stokes et al [19]. The BrainRuler software [20] is used to determine the cortical distance.

### Comparator

The comparator consists of 6 weeks of standard rTMS treatment, following the Dutch depression treatment guidelines [21]. This involves delivering a total of 90,000 magnetic pulses across 30 sessions (1 session per day), using 10 Hz stimulation at 120% of the resting motor threshold. Stimulation is applied to the left DLPFC, localized using the Beam-F3 method [16,22], which identifies the DLPFC based on standardized skull measurements.

### Image Acquisition and Preprocessing

Whole brain structural and functional images are acquired within 2 weeks before treatment and within 2 weeks after treatment. Scans will be performed on a 3-T whole-body scanner with standardized and optimized sequences. Sequences included in the pre- and posttreatment scans are described in Textbox 1.

Preprocessing of the functional and structural images is performed using the Freesurfer software suite, fMRIprep, an MRI quality control tool, and the FMRIB software library suite. Functional images are denoised and smoothed for stimulation target identification. Denoising was performed using global signal regression, 6 motion correction parameters, 8 physiological regressors, and spike removal. Smoothing was applied with a 6-mm full width at half maximum kernel.

Sequences included in the pre- and posttreatment scans.Pretreatment scansT1-weighted structural MRI (5 min): repetition time (TR)=2300 ms, echo time (TE)=2.26 ms, 192 slices, slice thickness=1.0 mm, voxel size=1×1×1 mm, and flip angle=8°Resting state–functional MRI (2×10 min): TR=1200 ms, TE=30 ms, 64 slices, slice thickness=2.0 mm, 488 volumes, voxel size=2×2×2 mm, Simultaneous Multi-Slice (SMS) factor=4, and flip angle=66°Diffusion tensor imaging (8 min): TR=3100 ms, TE=102 ms, 66 slices, slice thickness=2.0 mm, voxel size=2×2×2 mm, and SMS factor=3Tower of London task functional MRI (5.5 min): TR=1200 ms, TE=30 ms, 64 slices, slice thickness=2.0 mm, 488 volumes, voxel size=2×2×2 mm, SMS factor=4, and flip angle=66°Hariri Emotion Recognition task functional MRI (5.5 min) [23]: TR=1200 ms, TE=30 ms, 64 slices, slice thickness=2.0 mm, 488 volumes, voxel size=2×2×2 mm, SMS factor=4, and flip angle=66°Total scanning time=44 minutesPosttreatment scansT1-weighted structural MRI (5 min): TR=2300 ms, TE=2.26 ms, 192 slices, slice thickness=1.0 mm, voxel size=1×1×1 mm, and flip angle=8°Resting state–functional MRI (1×10 min): TR=1200 ms, TE=30 ms, 64 slices, slice thickness=2.0 mm, 488 volumes, voxel size=2×2×2 mm, SMS factor=4, and flip angle=66°T2-weighted fluid attenuated inversion recovery structural MRI (6 min): TR=5000 ms, TE=386 ms, inversion time=1650 ms 176 slices, slice thickness=1.0 mm, and voxel size=1×1×1 mmDiffusion tensor imaging (8 min): TR=3100 ms, TE=102 ms, 66 slices, slice thickness=2.0 mm, voxel size=2×2×2 mm, and SMS factor=3Tower of London task functional MRI (5.5 min): TR=1200 ms, TE=30 ms, 64 slices, slice thickness=2.0 mm, 488 volumes, voxel size=2×2×2 mm, SMS factor=4, and flip angle=66°Hariri Emotion Recognition task functional MRI (5.5 min): TR=1200 ms, TE=30 ms, 64 slices, slice thickness=2.0 mm, 488 volumes, voxel size=2×2×2 mm, SMS factor=4, and flip angle=66°Total scanning time=40 minutes

### Outcome Measures

#### Main Study Parameter or End Point

Remission of depression 1 week after the last treatment session was defined as a score of ≤7 on the 17-item Hamilton Depression Rating Scale (HDRS‐17).

#### Secondary Outcomes

In addition to the primary outcomes, secondary outcomes will be assessed to provide a more comprehensive understanding of the effectiveness and impact of rTMS/PAiT. First, an economic evaluation based on the general principles of a cost‐effectiveness (utility) analysis, which will be performed alongside the intervention by comparing patients treated with PAiT with those receiving standard 10 Hz rTMS. In addition, societal costs and health consumption will be assessed for the economic evaluation at baseline and 7, 12, and 26 weeks after baseline. We will use health‐related quality of life determined with the EQ‐5D‐5L and health care use or costs, patients’ and their family’s out‐of‐pocket costs, and productivity losses owing to absenteeism measured with the Trimbos Institute and Institute for Medical Technology Assessment Cost questionnaire for Psychiatry [24]. Second, patient‐reported outcome measures will be recorded, that is, positive mental health, as measured with Mental Health Continuum‐Short Form [25] and subjective memory loss. Third, percentage reduction of depressive symptoms will be measured with self‐rated 9-item Patient Health Questionnaire (PHQ-9) on each treatment day and the HDRS‐17. Fourth, relapse will be measured at 6 and 25 weeks after treatment. Relapse was defined as an HDRS‐17 total score of ≥15 for 2 consecutive assessments separated by 5 to 15 days or hospitalization for depression. Fifth, we establish tolerability of the treatment and side effects of PAiT and rTMS [9]. Sixth, we will identify health care system–, clinician‐, and patient‐related factors that influence the implementation of PAiT were identified to inform the development of an implementation plan. Seventh, we will compare patient-reported changes in mood 1 week after treatment (as measured with self-rated PHQ-9) with clinician-reported clinical impression (as measured with Clinical Global Impression [23]).

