### Participants

We aim to include 108 adult patients diagnosed with moderate to severe (Hamilton Depression Rating Scale >16) unipolar major depressive disorder without psychotic symptoms and who have had a failed response to at least 2 treatment trials with adequately dosed antidepressants or evidence-based forms of psychotherapy (interpersonal therapy, cognitive behavioral analysis system of psychotherapy, behavioral therapy, cognitive behavioral therapy, cognitive bibliotherapy, problem‐solving therapy, brief psychodynamic therapy, and reminiscence therapy). Exclusion criteria include lifetime diagnosis of bipolar disorder, current psychotic disorder, substance abuse disorder, suspected dementia, active suicidal thoughts with intent to act on them, patients with epilepsy, patients with large or ferromagnetic metal parts in the head (except for a dental wire), implanted cardiac pace maker or neurostimulator, or inability to understand or comply with study requirements.

These exclusion criteria serve 2 purposes: first, to ensure a clinically homogeneous sample of patients with unipolar depression, free from comorbid conditions that could affect treatment effectiveness; and second, to comply with safety guidelines related to rTMS, the accelerated iTBS protocol, and the required magnetic resonance imaging (MRI) procedures, as well as general safety standards.

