For the Percentual reduction of depressive symptoms, as measured with self‐rated PHQ-9 on each day using the PAiT protocol, compared to weekly reduction of depressive symptoms, as measured with PHQ-9 during standard 10 Hz rTMS we will use linear mixed models. Similarly, we will determine percent reduction of depressive symptoms, as measured with the clinically assessed HDRS‐17 before, during, and after treatment, as well as at the follow-up moments.

Relapse, at 6 and 25 weeks after treatment, defined as (1) sustained remission, that is, HDRS-17≤7, and (2) sustained response, that is, response at end of treatment maintained through week 6 and 25. During treatment phase (T2), we will conduct the HDRS-17 weekly for 6 weeks for both treatment arms. By doing this, using the chi-square test, we can compare the remission rate with PAiT after 6 weeks to 6 weeks of treatment with standard 10 Hz rTMS; this is of interest as patients allocated to PAiT only receive treatment for 1 week.

We will report the prevalence of side effects during and directly after treatment based on international recommendation [17]. We will establish the tolerability and side effects of PAiT and rTMS. We will use qualitative data collected while supporting the implementation of PAiT, to analyze health care system–, patient‐, and clinician‐related factors that influence the implementation of PAiT in clinical settings. We will use a 1-tailed paired *t* test or an ANOVA to compare patient-reported changes in mood 1 week after treatment (as measured with self-rated PHQ-9) with clinician-reported clinical impression (as measured with the Clinical Global Impression scale).

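### The relapse rule requires no earlier remission or response, so patients who never remit and stay at HDRS-17 ≥15 count as relapses as written

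*Protocol article*

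**What the plan says.** The article describes relapse in two places.

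- **Secondary Outcomes** gives the timing, "relapse will be measured at 6 and 25 weeks after treatment", and the rule: "Relapse was defined as an HDRS‐17 total score of ≥15 for 2 consecutive assessments separated by 5 to 15 days or hospitalization for depression". It states no earlier remission or response and no set of patients at risk.
- **Secondary Study Parameters** (Statistical Analyses) uses the same name differently: "Relapse, at 6 and 25 weeks after treatment, defined as (1) sustained remission, that is, HDRS-17≤7". A second limb, sustained response, is "response at end of treatment maintained through week 6 and 25". Only this second limb expressly depends on status at the end of treatment.

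Three other statements bear on the point.

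- **Participants** admits patients with "Hamilton Depression Rating Scale >16". I take this to be the 17-item version used elsewhere.
- **Main Study Parameter or End Point** sets the primary outcome: "Remission of depression 1 week after the last treatment session was defined as a score of ≤7" on the HDRS-17.
- The **Overview** of the Statistical Analyses names the intention-to-treat and per-protocol samples and makes no exception for relapse.

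**The concern.** Relapse is the return of illness after improvement. The rule under Secondary Outcomes is an absolute score level, and every patient starts above it. A patient who scores 22 at baseline and 20 at each later rating has not responded, yet meets the rule.

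The sustained-remission limb has a milder form of the same gap. Its only operational content is a score of 7 or less, and it is not tied to the 1-week visit where the primary outcome is recorded.

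The section on durability raises the possibility that PAiT follows the course seen with ECT: fast benefit, then frequent relapse. The abstract's conclusions and Relevance for Practice promise insight into relapse. If non-response is counted as relapse, the arm with more remitters tends to show fewer relapses for that reason alone. The risk that the authors name could then go unseen.

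**Working it through.** **Inputs from the article (Sample Size Calculations).** Remission is 55% with PAiT and 25% with rTMS; 108 patients are randomized, so about 54 per arm. No figure is given for relapse. The stated size does reproduce: 25% vs 55%, two-sided 5%, 80% power, pooled variance and no continuity correction gives 41 per arm, or 82; and 82 × 1.32 = 108.24.

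**Assumed inputs (not in the article).**
- f: share of patients not in remission at 1 week who later score ≥15 twice. A simulation with mean scores of 14 to 18, true-score SD 5 and rating SD 2 to 3 gave 0.40 to 0.69; those settings are also assumptions.
- q: relapse risk among 1-week remitters, first taken as equal in both arms.

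**Literal count in all randomized patients.** For an arm with remission rate p, the rate is (1 − p)f + pq.
- PAiT: 0.45f + 0.55q
- rTMS: 0.75f + 0.25q
- rTMS minus PAiT: 0.30f − 0.30q = 0.30(f − q)

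| f | q | PAiT | rTMS | Difference |
|---|---|---|---|---|
| 0.4 | 0.2 | 29% | 35% | 6 points |
| 0.7 | 0.2 | 42.5% | 57.5% | 15 points |
| 0.9 | 0.1 | 46% | 70% | 24 points |
| 0.5 | 0.5 | 50% | 50% | 0 |
| 0.3 | 0.5 | 41% | 35% | −6 points |

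At f = 0.7 and q = 0.2, non-remitters supply 0.315/0.425 = 74% of the counted relapses in PAiT and 0.525/0.575 = 91% in rTMS.

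**Can a real excess be hidden?** Let 40% of PAiT remitters and 20% of rTMS remitters relapse.
- PAiT: 0.45f + 0.55 × 0.40 = 0.45f + 0.22
- rTMS: 0.75f + 0.25 × 0.20 = 0.75f + 0.05
- Difference: 0.30f − 0.17, which favours PAiT once f exceeds 0.17/0.30 = 0.57

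At f = 0.7 the rule reports 53.5% vs 57.5%, in favour of PAiT. At f = 0.5 it reports 44.5% vs 42.5%, so a 20-point excess among remitters shrinks to 2 points.

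**Restricting to 1-week remitters.** The difference is zero when q is equal in both arms. The groups are 54 × 0.55 = 29.7 and 54 × 0.25 = 13.5, about 30 and 14 patients, selected after randomization.

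**Sustained remission in all randomized patients.** If only those who relapse lose remission, the rates are p(1 − q), and the arms differ by 0.30(1 − q) when q is equal: 44% vs 20% at q = 0.2. With remitter relapse of 40% and 20%, they are 0.55 × 0.60 = 33% and 0.25 × 0.80 = 20%. Remitters who drift to 8–14 would lower these rates further.

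**The case against.** The best defence is that the words relapse and sustained both presuppose earlier improvement, that the durability section uses relapse in that sense, and that the sustained-response limb says so outright. The intention is probably sound. This stands for sustained remission, which is under-specified rather than wrong. It does not rescue the ≥15 rule, which is spelled out down to the interval between ratings and still omits the condition.

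A second defence is that no sentence assigns relapse to all randomized patients, and that analysis sets are often left to a fuller document. But the Overview names the samples for the statistical analyses without exception. The only completeness rule in the article concerns missed sessions, so a per-protocol sample built on it would not remove non-remitters.

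A reader might go further and infer that all non-remitters become relapses, or that the relapse comparison mostly repeats the primary outcome. The article does not support either. Non-remitters scoring 8–14 do not meet the rule. A non-remitter above 7 fails the sustained-remission limb, so that limb creates no false relapses. The carry-over depends on f and q and can be zero or negative.

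Nor does the case f = 0.4, q = 0.2 show a reversal. Relapses among remitters would be 11% and 5% of all patients, against a reported 29% and 35%, but the risk among remitters is the same in both arms, so no true excess is being reversed.

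The visit schedule also limits the arithmetic. After week 7, visits are at weeks 12, 26 and 31, so ratings 5 to 15 days apart are not scheduled around 25 weeks in either arm, or around 6 weeks after rTMS (week 12). PAiT has weekly ratings up to its 6-week point (week 7). The formula assumes that pairs are available in both arms; on scheduled visits alone, size and direction could differ.

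**Conclusion.** The point holds for the relapse rule under Secondary Outcomes. As written it counts persistently ill non-remitters, and in an intention-to-treat count it mixes failure to remit with loss of remission. At the planned remission rates the distortion is 0.30(f − q): 6 to 15 points in favour of PAiT for f of 0.4 to 0.7 with q = 0.2, and none at f = q. A true excess after PAiT can be masked, as in the 53.5% vs 57.5% example.

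These sizes rest on assumed f and q, on the planned remission rates, and on rating pairs being available in both arms. The rule's omission does not depend on any of them. The primary outcome is unaffected. This is a secondary outcome that should be corrected before analysis.

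**What to change.** 1. Reconcile the two sections so that relapse has one definition and is not equated with sustained remission or response. State which ratings supply the required pair.
2. Count relapse only in patients with HDRS-17 ≤7 at the 1-week primary visit.
3. Define sustained remission as ≤7 at that visit and at the later visit.
4. Make the randomized comparison on sustained remission in all randomized patients, with those not in remission at 1 week counted as not achieving it. Call it sustained remission, not relapse, because it too carries the primary difference.
5. Beside it, report relapse among 1-week remitters by arm, descriptively and marked as a non-randomized comparison.

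The cost is one or two sentences and one derived variable. Sustained remission uses ratings already scheduled. The downside is that it mixes achieving and keeping remission, so it cannot by itself show excess relapse; the descriptive figure is needed for that and will be imprecise at about 30 and 14 patients.

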### Study Design

This multicenter single‐blind RCT consists of 2 phases in which participants will be randomly assigned to either standard 10 Hz rTMS (30 daily rTMS sessions in 6 weeks, providing a total of 90,000 magnetic pulses) or PAiT (50 iTBS sessions in 5 days, providing a total of 90,000 pulses) [11,12], with 4 follow‐up moments at 7, 12, 26, and 31 weeks after baseline. In either condition, the timing of these measurements translates to clinically relevant time points at 6 and 25 weeks after treatment, as well as aligned postbaseline follow-ups that are important for the cost-effectiveness analysis. As such, the follow-up measurement at 31 weeks after baseline is only used in the rTMS condition (25 weeks after treatment).

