### Study Procedures

Study information is provided to eligible participants, and these patients are contacted again after at least 7 days to discuss participation and any remaining questions. If patients choose to participate, they will be invited to a research intake session, during which they will sign the informed consent form and undergo screening for inclusion and exclusion criteria. Participation is voluntary, and individuals may withdraw from the study at any time. Table 1 shows an overview of the study. Participants who were allocated to standard 10 Hz rTMS will be offered PAiT after the end of the study (eg, 25 weeks after the last rTMS session). We will request patients allocated to PAiT to postpone enrolling in standard 10 Hz rTMS for 25 weeks after the last treatment session. This is merely a request as patients are allowed to ask for treatment as usual, including standard 10 Hz rTMS. Our participating treatment centers deem it not ethical to withhold this usual 10 Hz rTMS treatment upon a patient’s request. In addition to clinical effectiveness, we will study patient‐reported outcomes, tolerability, and safety. Alongside this RCT, we will also conduct an economic evaluation and evaluate facilitating and hindering factors related to implementation in the group of researchers and health care professionals involved in this study. The funding agency, the Efficiency Studies arm of the Care Research Netherlands and Medical Sciences of the Dutch Research Council, has explicitly requested that the trial be based in care as usual.

**Table 1 table1:** An overview of the study for both treatment conditions.

			rTMS^a^		PAiT^b^
**T0**					
	Week –2	Screening: clinicometrics; biobank; MRIc pre+additional tasks; rTMS premeasurements		Screening: clinicometrics; biobank; MRI pre+additional tasks; PAiT premeasurements	
**T1**					
	Week 0	Baseline		Baseline	
**T2**					
	Week 1	Treatment Clinicometrics (weekly)		Treatment Clinicometrics (daily)	
	Week 2	Biobank		Follow-up (1 week): clinicometrics (weekly); MRI post+additional tasks; biobank	
	Week 6	Clinicometrics		Clinicometrics	
**T3**					

	Week 7	Follow-up: clinicometrics; MRI post+additional tasks; biobank		Follow-up: clinicometrics; biobank	
**T4**					
	Week 12	Follow-up: clinicometrics; biobank		Follow-up: clinicometrics	
**T5**					
	Week 26	Follow-up: clinicometrics		Follow-up (25 weeks): clinicometrics	
**T6**					
	Week 31	Follow-up (25 weeks): clinicometrics		Clinicometrics	

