### Blinding

Participants and those who will be administering the rTMS or PAiT treatment cannot be blinded. Those carrying out clinical assessments will be blinded. Blind rating will be carried out via video-recorded interviews with participants. Interviewers will not be blinded to the treatment conditions and, therefore, will be thoroughly instructed to carry out the interview in a structured and objective manner. A blinded rater will score the videotaped clinical assessments. To ensure minimal bias effects, 20% (227/1134) of interviews will be randomly assessed on interrater reliability and interview quality. All video footage will be deleted after rating the interviews and after the independent monitor has reviewed and agreed. The clinical ratings will be stored for further analysis.

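### Relapse is defined in two incompatible ways, and the HDRS part of one definition can be met on the visit schedule at 6 weeks after treatment only in the PAiT arm and at 25 weeks in neither arm

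*Protocol article*

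**What the plan says.** Secondary Outcomes in the protocol article states that "relapse will be measured at 6 and 25 weeks after treatment". It sets the criterion as an HDRS-17 score of at least 15 "for 2 consecutive assessments separated by 5 to 15 days or hospitalization for depression".

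Secondary Study Parameters, under Statistical Analyses, returns to the same outcome at the same time points with a different definition: "Relapse, at 6 and 25 weeks after treatment, defined as (1) sustained remission", followed by sustained response as a second element. Remission there means HDRS-17 of 7 or less.

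On timing, Study Design lists follow-up "moments at 7, 12, 26, and 31 weeks after baseline" and says that the week 31 visit is used only for rTMS. Table 1 nevertheless shows clinicometrics for PAiT at week 31. Secondary Study Parameters plans weekly HDRS-17 ratings for 6 weeks in both arms, and the section on challenges of the trial extends weekly clinical measurement to 7 weeks. The article mentions no second, confirmatory rating at any later visit. The Blinding section gives the total number of interviews: "20% (227/1134) of interviews will be randomly assessed on interrater reliability and interview quality".

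**The concern.** There are two separate problems.

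First, the two sections attach one name to opposite states. They are not complements either: a patient scoring 8 to 14 is neither in remission (7 or less) nor relapsed (15 or more). Two analysts, each following one section, would report different quantities as relapse.

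Second, the HDRS part of the Secondary Outcomes rule needs two consecutive ratings 5 to 15 days apart. The arms finish treatment at different times, while the weekly ratings stop at the same time after baseline. The opportunity to meet the rule after treatment therefore differs by arm.

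Durability is one of the trial's stated interests. The section on durability of effects raises the possibility of early relapse after a short intensive course, and the article's conclusions promise information on relapse. A rule that can detect symptomatic relapse in one arm and not in the other would undermine that comparison.

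**Working it through.** **Inputs.** PAiT lasts 1 week and rTMS 6 weeks (Cost-Effectiveness). Ratings are weekly to week 7, then at weeks 12, 26 and 31 (Study Design, Table 1, Challenges of the Proposed Trial). Relapse time points are 6 and 25 weeks after treatment. The permitted spacing is 5 to 15 days.

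**Reproducing the stated interview total.** Assume 54 patients per arm (1:1 allocation of 108).
- PAiT: one pretreatment rating + weeks 1 to 7 + week 12 + week 26 = 1 + 7 + 1 + 1 = 10.
- rTMS: the same plus week 31 = 11.
- 54 × 10 + 54 × 11 = 540 + 594 = 1134, the stated figure; 20% of it is 226.8, given as 227.

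Other counts do not reproduce it. Week 31 in both arms gives 54 × 11 × 2 = 1188. Week 31 in neither arm gives 54 × 10 × 2 = 1080. Two pretreatment ratings (screening and baseline), with week 31 in rTMS only, give 54 × 11 + 54 × 12 = 1242.

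**Gaps between consecutive scheduled ratings** (weeks × 7 days):

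| Pair of weeks | Gap | Within 5 to 15 days? |
|---|---|---|
| each pair from 1/2 to 6/7 | 7 days | yes |
| 7/12 | 5 × 7 = 35 days | no |
| 12/26 | 14 × 7 = 98 days | no |
| 26/31 | 5 × 7 = 35 days | no |

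To reach 15 days, the last three gaps would have to shrink by 20, 83 and 20 days, more than an ordinary visit window.

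**Applying the rule at each time point:**

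| Time after treatment | Arm | Visit | Preceding rating | HDRS part can be met? |
|---|---|---|---|---|
| 6 weeks | PAiT | 1 + 6 = week 7 | week 6, 7 days earlier | yes |
| 6 weeks | rTMS | 6 + 6 = week 12 | week 7, 35 days earlier | no |
| 25 weeks | PAiT | 1 + 25 = week 26 | week 12, 98 days earlier | no |
| 25 weeks | rTMS | 6 + 25 = week 31 | week 26, 35 days earlier | no |

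**Cumulative reading.** If relapse by 6 weeks means any qualifying pair since the end of treatment, PAiT has six such pairs (weeks 1/2 to 6/7) and rTMS has one (weeks 6/7). The imbalance has the same direction.

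**Table 1 discrepancy.** If PAiT is also rated at week 31, the pair 26/31 is still 35 days apart, so nothing changes.

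**The case against.** A reader might infer that relapse as such cannot be detected at 25 weeks, or in rTMS at 6 weeks. The documents do not support that. The Secondary Outcomes rule also counts hospitalization for depression, which does not depend on visit spacing and can register in either arm at any time. Only the HDRS part fails.

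A reader might also infer that the published comparison will be an artefact of visit spacing. That does not follow either. The analysis text uses sustained remission and sustained response, and both can be scored from the single scheduled visits in each arm. The bias arises only if the Secondary Outcomes rule is the one analysed, and the article does not settle this.

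The match to 1134 should not be read as proof that no confirmatory ratings are planned. It depends on counting one pretreatment rating and on leaving out PAiT at week 31, whereas Table 1 lists both a screening and a baseline contact and also shows PAiT at week 31. A rating triggered by a high score would not normally enter a fixed total, and the full protocol may describe one. The match is suggestive only.

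Later treatment is a separate matter. Study Procedures asks PAiT patients to postpone standard rTMS but adds: "This is merely a request as patients are allowed to ask for treatment as usual, including standard 10 Hz rTMS". How this is handled in the sustained outcomes may properly be left to an analysis plan, and it forms no part of this point.

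Finally, relapse is the fourth of seven secondary outcomes. The primary endpoint, its test and the sample size do not depend on it. That stands, and it limits the severity. None of these objections removes the contradiction between the two sections or the gaps in the schedule.

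**Conclusion.** The point holds in limited form. The two definitions are incompatible as written. On the scheduled ratings, the HDRS part of the Secondary Outcomes rule can be met in one of two arms at 6 weeks after treatment and in neither arm at 25 weeks. Where it cannot be met, only hospitalization can register a relapse. If that rule is analysed, symptomatic relapse at 6 weeks would be counted preferentially in PAiT.

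The size is best expressed as opportunities for detection: six qualifying post-treatment pairs in PAiT against one in rTMS. It cannot be given in percentage points, because the article states no relapse rate.

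The conclusion assumes visits close to their nominal weeks and no unscheduled confirmatory ratings. The article mentions none, and its interview total is consistent with none, but neither fact proves it. This is a secondary-outcome defect that should be fixed; the primary analysis is not touched.

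**What to change.** Reconcile Secondary Outcomes, Secondary Study Parameters and the visit schedule before analysis.

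1. Remove the wording in Secondary Study Parameters that defines relapse as sustained remission and sustained response. Report these two as separately named outcomes in all randomized patients.
2. Define relapse so that both arms are scored identically at matched visits: PAiT weeks 7 and 26, rTMS weeks 12 and 31. Among patients in remission or response at the rating one week after treatment, count HDRS-17 of 15 or more at the matched visit, or hospitalization for depression since the end of treatment.
3. Keep the condition of prior remission or response. Patients enter with a score above 16, so without it a patient who never improved would count as relapsed.
4. That subset is formed after randomization, so present the relapse comparison as descriptive, beside the sustained outcomes in all randomized patients.

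The cost is a change of wording, using ratings already planned. The drawback is that a single-visit criterion is less specific than a confirmed one. If the full protocol does provide confirmatory ratings in both arms, keeping the two-rating rule and stating those ratings would also reconcile the definition with the schedule; step 1 would still be needed.
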